## Methods

### Study design

The global HCC BRIDGE study is a multiregional longitudinal cohort trial including patients diagnosed with HCC from January 1, 2005, to June 30, 2011 [10]. Patients enrolled in the study will be followed from the date of HCC diagnosis to December 31, 2011, or date of death, whichever comes first. The HCC BRIDGE China national study comprises the portion of the global HCC BRIDGE study conducted within mainland China. To ensure that the national study is geographically representative, it was designed to include patients enrolled at sites from all 7 traditional regions across China (North, North-East, East, South, South-West, North-West, and Central).

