**Primary end point**
Overall survival
Number of days from date of treatment initiation to date of death. Death will be verified by sites based on death certificates or via caregiver, relative, or health care provider, and death information source will be captured in data collection. Surviving patients will be censored from last date of treatment assessment.

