**Secondary end points**
Disease progression
Number of patients by treatment intervention with MRI/CT evidence of visible arterial enhancement, radiologic report of progression, or radiologic report of new tumor growth or symptomatic/clinical progression.
Time to disease progression
Number of days from date of treatment initiation to date of documented disease recurrence based on MRI or CT by treatment intervention, or symptomatic/clinical progression. Patients without recurrence will be censored from last date of treatment assessment.
Complication rate
Number of patients by treatment intervention who were withdrawn due to adverse events prior to introduction of other therapy.
Time to treatment-limiting adverse events
Number of days from first date of treatment to date of withdrawal due to adverse event(s) prior to introduction of other therapy. Patients without treatment-limiting adverse events will be censored at last date of treatment assessment.
Treatment failure rate
Number of patients by treatment intervention with a finding of treatment switch, HCC-related hospitalization and emergency room visit, disease recurrence, or death prior to introduction of other therapy.
Time to treatment failure
Number of days to first treatment failure overall and by individual item. Patients without treatment failure will be censored from last date of treatment assessment.

CT, computed tomography; MRI, magnetic resonance imaging.

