### Data collection

The following data will be systematically collected for all enrolled patients: (1) date of diagnosis and/or date of first HCC visit; (2) demographic and clinical characteristics at the time of diagnosis/first HCC visit and at all occurrences of new treatment intervention during the study period via medical chart review; (3) data on variants of HCC diagnosis, for example, mixed HCC, fibrolamellar HCC, and on the additional diagnosis of cholangiocarcinoma; (4) data on the use of currently available HCC treatment approaches during the study period from medical chart review; (5) data on the use of new treatments for HCC if they become available and are used prior to study end; (6) data on hospitalizations, clinical visits, and visits to other health care professionals, with collection of hepatic function, tumor assessments, and laboratory values according to clinical judgment; and (7) data on method of payment for health care utilization. All data will be collected retrospectively and prospectively at study sites in order to account for patient records over the full duration of the study; data collection is expected to be complete by June 2012. All sites will enter data into an electronic data capture system developed by Outcome Sciences, Inc. (Cambridge, MA, USA). Outcome Sciences will manage the data system, including monthly data monitoring and cleaning, site queries, and check of invalid clinical values determined a priori by study investigators. All data collection procedures will comply with Chinese privacy and confidentiality requirements.

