### Data analysis

To evaluate therapeutic approaches to HCC in China, the number and percentage of patients using each treatment (plus any new treatments that are approved and used within the study period) will be determined for each study year, in total and stratified by disease stage and site. Treatment patterns will also be assessed by disease stage for each study year. Patient characteristics will be stratified by disease stage and by site for each study year.

To assess therapeutic outcomes, age- and gender-adjusted rates will be calculated for each study end point. Cox proportional hazard models will be used for the time-to-event end points (overall survival and disease progression) to determine hazard ratios for each treatment approach, and Kaplan-Meier curves will be generated. Logistic regression models will be used for categorical end points (treatment-limiting adverse events and treatment failure). Covariates for the models will include disease stage, gender, age, duration of disease, etiology of disease, liver status, tumor size/spread, surgical intervention/number of interventions, and number of comorbidities; analyses will be conducted at the site and country level. The same analysis plan will be adopted for the evaluation of survival and other clinical end points with sorafenib versus other therapies, except that "treatment" will be included as a covariate. Further analyses will be conducted to evaluate clinical characteristics and demographics of patients treated with sorafenib versus other treatments for HCC. In addition, data collected will be used to analyze additional aspects related to HCC epidemiology and management in China (Table 2). All tests of statistical significance will be carried out at the 0.05 level.

**Table 2 T2:** Additional aspects of HCC management for potential evaluation using data from the HCC BRIDGE China national study.

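### Time to treatment-limiting adverse events: the event can occur only before another therapy starts, but the censoring rule does not stop the clock there

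*Protocol article*

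**What the plan says.** In the protocol article, End points, Table 1, the row for time to treatment-limiting adverse events has two sentences. The first defines the event: "Number of days from first date of treatment to date of withdrawal due to adverse event(s) prior to introduction of other therapy". The second defines censoring: "Patients without treatment-limiting adverse events will be censored at last date of treatment assessment". The companion count, the complication rate, uses the same event window: "Number of patients by treatment intervention who were withdrawn due to adverse events prior to introduction of other therapy".

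For overall survival, Table 1 uses the same censoring phrase: "Surviving patients will be censored from last date of treatment assessment".

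Study design says that patients are "followed from the date of HCC diagnosis to December 31, 2011, or date of death, whichever comes first", with no exception for a change of treatment. Data collection gathers characteristics "at all occurrences of new treatment intervention during the study period via medical chart review".

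Data analysis names Cox models and Kaplan-Meier curves for overall survival and disease progression. For this end point it says: "Logistic regression models will be used for categorical end points (treatment-limiting adverse events and treatment failure". It also promises age- and gender-adjusted rates for every end point, without giving the denominator.

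**The concern.** The two sentences of this row do not fit together. Once another therapy begins, the patient can no longer have the event, because the definition excludes it. The censoring sentence does not remove the patient from the risk set at that moment.

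Take a patient who changes treatment in month 2 because of progression and is last assessed in month 24. If the clock runs to that assessment, the patient adds 24 − 2 = 22 months in which the event is impossible. This time enlarges the denominator and never the numerator.

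The more often and the earlier a treatment is switched for other reasons, the more such time it collects. A treatment could then look better tolerated partly because patients left it quickly. Differing switch rates are plausible: the treatments range from resection and ablation to chemoembolization and sorafenib. The protocol itself expects switching, since it counts it in another end point: "Number of patients by treatment intervention with a finding of treatment switch".

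**Working it through.** **What the censoring phrase means.** The document does not define it. Three places bear on it.

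1. Overall survival is censored with the same phrase. There it has to reach past a switch, or later survival time would be discarded.
2. Follow-up runs to death or the end of 2011, whatever treatment is given.
3. Data are collected at each new intervention, so assessments after a switch will exist.

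The natural reading is therefore the last assessment in follow-up.

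**Inputs.** The documents give no adverse-event withdrawal rate, switch rate or event count for this end point, so there is no figure of the plan to reproduce. All rates below are assumptions, chosen to show direction and range.

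**Closed form.** Let λ be the hazard of adverse-event withdrawal, s the hazard of switching for other reasons, h = λ + s, and T a common follow-up in months.

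- Events per patient: (λ/h)(1 − e^(−hT))
- Person-time if the clock stops at the switch: (1 − e^(−hT))/h
- Person-time as written: T − λ[T/h − (1 − e^(−hT))/h²]

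With λ = 0.02 per month in both treatments and T = 24:

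| | Late-switched, s = 0.02 | Early-switched, s = 0.15 |
|---|---|---|
| Events per patient | 0.3086 | 0.1157 |
| Person-months, clock stopped at switch | 0.6171/0.04 = 15.43 | 0.9831/0.17 = 5.78 |
| Person-months, as written | 24 − 0.02(600 − 385.7) = 19.71 | 24 − 0.02(141.2 − 34.0) = 21.86 |
| Rate, clock stopped at switch | 0.0200 | 0.0200 |
| Rate, as written | 0.0157 | 0.0053 |

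The rate ratio, early versus late, is 1.00 with the clock stopped at the switch and 0.34 as written. For λ from 0.01 to 0.05 with the same switch rates, the written rule gives 0.51 to 0.52 at 12 months and 0.34 at 24 months.

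**Cox simulation.** 20,000 patients per group, censoring uniform between 6 and 24 months, λ = 0.02 in both groups, s = 0.02 in the late-switched group, true hazard ratio 1:

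| s in early-switched group | Hazard ratio as written | Hazard ratio, clock stopped at switch | Logistic odds ratio |
|---|---|---|---|
| 0.02 | 0.99 | 0.98 | 0.99 |
| 0.05 | 0.80 | 1.01 | 0.78 |
| 0.10 | 0.59 | 1.01 | 0.55 |
| 0.15 | 0.46 | 1.04 | 0.42 |

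If the early-switched treatment is truly worse (λ = 0.03 against 0.02, hazard ratio 1.5; s = 0.15 against 0.02), stopping at the switch gives 1.53 and the written rule gives 0.68. The direction reverses.

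A second set of assumptions agrees: λ = 0.05 in both groups, s = 0.05 in the reference group, last assessment exponential with mean 18 months capped at 48. The written rule gives 0.72 at s = 0.10 and 0.46 at s = 0.20, against 0.99 and about 0.97 to 0.98 with the clock stopped at the switch. With equal switching both rules give 1.00.

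The logistic column leans the same way, but for another reason: early-switched patients have less time in which the event can occur. No censoring date enters that model.

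**The case against.** **The named model does not use this rule.** This is the strongest point, and it stands. Data analysis assigns logistic regression to treatment-limiting adverse events, and Cox models only to overall survival and progression. A reader might infer that the planned treatment comparison would return a hazard ratio such as 0.46. The document does not support that: no Cox model is named here, and correcting the censoring leaves the logistic result as it was. Nor are the promised adjusted rates certain to be affected, since their denominator is not given and the rate rows of Table 1 are worded as counts. What remains is narrower. Table 1 defines a separate time-to-event end point with its own censoring rule, and any summary of it, or any person-time rate, inherits the mismatch.

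**The phrase may mean the last assessment on that treatment.** For an end point reported per treatment this is a reasonable reading, and it would largely remove the problem. A reader might also take the longer reading as certain, and the text does not settle that. The use for overall survival points to it, and under either intention the sentence needs clearer wording.

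**Keeping switched patients at risk is a recognised approach.** It matches the risk set of a subdistribution hazard, which is a valid route to the cumulative incidence of adverse-event withdrawal before a switch. That is correct, so the written rule is wrong only as a measure of the on-treatment hazard. But the document states no such aim and does not call switching a competing event.

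**An article condenses.** Derivations are commonly left to the full protocol or analysis plan. Here, however, the article does state the censoring rule, and the rule does not fit the event defined beside it.

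**Conclusion.** The concern holds in a limited form. On the natural reading, the censoring rule keeps switched patients at risk when the event is impossible. Time-to-event summaries and person-time rates of this secondary end point would then understate the on-treatment hazard, most for treatments switched early. Confidence is moderate, because the phrase is undefined.

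The size cannot be derived from the documents. Hazard ratios of about 0.46 to 0.80 instead of 1 rest on assumed constant hazards, on switching independent of adverse-event risk, and on switch rates 2.5 to 7.5 times higher in one treatment than in the other (0.05 to 0.15 against 0.02 per month). With equal switch rates the ratio between treatments stays at about 1. The primary end point and the logistic analysis are not affected by this rule.

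**What to change.** Replace the censoring sentence in this row of Table 1 with wording to this effect: *a patient with no treatment-limiting adverse event is censored on the date another therapy is introduced or on the date of the last assessment, whichever is earlier.* State that the resulting hazard is cause-specific, that is, on treatment. For cumulative proportions, treat introduction of other therapy and death as competing events and report cumulative incidence.

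The cost is one sentence and one derivation. Data are already to be collected at each new treatment intervention.

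There are two downsides. Person-time for this end point falls, though what is lost is time in which no event could be counted. Censoring at the switch may also be informative if switching is related to tolerability, which is why the cumulative incidence should stand beside the hazard. The change does not remove the effect of shorter exposure on the logistic regression.

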## Background

Hepatocellular carcinoma (HCC), one of the world's most prevalent and deadly malignancies [1,2], is particularly common in Asia-Pacific countries, with more than half of all cases occurring in China alone [2,3]. In most patients, HCC develops in association with liver cirrhosis and/or viral hepatitis infection. Indeed, the main risk factors for the development of HCC among the Chinese population are the presence of liver cirrhosis and chronic infection with hepatitis B virus [4]. Other risk factors include chronic hepatitis C virus infection, a family history of liver cancer, depression, ingestion of aflatoxin B1 via contaminated foodstuffs, and excessive alcohol consumption [4,5].

Current therapeutic options for HCC in China are varied, with treatment allocation generally dependent on the patient's liver function and tumor burden. Commonly used therapies include surgical techniques, such as liver resection and liver transplantation; interventional therapies, such as hepatic artery infusion and transcatheter arterial chemoembolization; and ablation techniques, such as anhydrous alcohol injection and radiofrequency or microwave ablation [6]. Systemic therapy options, including radiotherapy, immunotherapy, standard chemotherapy, and traditional Chinese herbal medicines, are also recommended [6]. In addition, the multikinase inhibitor sorafenib, which has demonstrated a reduction in death risk among advanced, inoperable HCC patients with mostly Child-Pugh A cirrhosis [7,8], is approved in China for treatment of advanced unresectable HCC.

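### The treatment-failure definition in Table 1 does not exempt admissions that deliver or repeat the index treatment, nor say whether hospitalization and emergency visit are alternatives, so it is unsound for comparing treatments

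*Protocol article*

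**What the plan says.** In the protocol article, Table 1 (secondary end points), the treatment failure rate row opens "Number of patients by treatment intervention with a finding of treatment switch" and goes on to "HCC-related hospitalization and emergency room visit, disease recurrence, or death prior to introduction of other therapy". The only limit on what counts is the last phrase, which closes the window when a different therapy starts. Nothing separates planned from unplanned admissions.

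The time to treatment failure row reads "Number of days to first treatment failure overall and by individual item" and gives no starting date. Overall survival and the other time-to-event rows of Table 1 do give one: treatment initiation or the first date of treatment.

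The Background lists the treatments in use. They include "surgical techniques, such as liver resection and liver transplantation", "interventional therapies, such as hepatic artery infusion and transcatheter arterial chemoembolization" and ablation. The Data collection section says that sites record "data on hospitalizations, clinical visits, and visits to other health care professionals", and mentions neither a reason for admission nor a planned/unplanned flag.

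The Data analysis section assigns logistic regression to treatment failure and then extends the approach to sorafenib: "The same analysis plan will be adopted for the evaluation of survival and other clinical end points with sorafenib versus other therapies".

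**The concern.** A failure event should show that the treatment did not work or could not be continued. An admission for a further session of the same procedure shows neither, but it is HCC-related on its face. A repeat session of the same treatment is not another therapy, so it falls inside the counting window.

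The outcome is binary and composite, so such an admission carries the same weight as a death. A treatment delivered through repeated inpatient sessions could then show a high failure rate because of how it is given. The treatment odds ratio for this end point would mix delivery setting with effectiveness.

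The word joining hospitalization and emergency visit adds a second uncertainty. Sites or programmers could read it as either or as both, and would then count different events.

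**Working it through.** **Step 1: the two readings, side by side.** The article states no failure rate, admission rate, effect size or power for this end point, so there is no figure to reproduce. The first check is logical.

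| Event before other therapy | Counted if the two items are alternatives | Counted if both are required |
|---|---|---|
| Planned inpatient repeat session, no emergency visit | yes | no |
| HCC-related emergency admission, no emergency room visit | yes | no |
| HCC-related emergency room visit, not admitted | yes | no |

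The first row should not be a failure and the second should be. Each reading gets one of the two wrong.

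**Step 2: possible size under the first reading.** All inputs are assumptions:
- p: failure probability with delivery admissions left out.
- q: share of otherwise non-failing patients with a counted delivery admission.
- Recorded failure = p + (1 − p)q.
- The odds ratio (OR) is the odds of recorded failure, sorafenib versus procedure.

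Take equal true failure (true OR 1.00), p = 0.5, q = 0.3 for the procedure and q = 0 for sorafenib:
- Procedure: 0.5 + 0.5 × 0.3 = 0.65, odds 0.65/0.35 = 1.857.
- Sorafenib: 0.50, odds 1.
- OR = 1/1.857 = 0.54.

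With q = 0 for sorafenib and other values of p and procedure q:

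| p | q = 0.1 | q = 0.3 | q = 0.5 | q = 0.9 |
|---|---|---|---|---|
| 0.3 | 0.73 | 0.41 | 0.23 | 0.03 |
| 0.5 | 0.82 | 0.54 | 0.33 | 0.05 |
| 0.7 | 0.86 | 0.62 | 0.41 | 0.07 |

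**Step 3: does the direction hold?** Keep p = 0.5 and let sorafenib patients have counted admissions too, at q = 0.3:
- Procedure q = 0.3: both groups record 0.65, so OR = 1.00.
- Procedure q = 0.1: recorded 0.55, odds 1.222, so OR = 1.857/1.222 = 1.52. The bias now runs against sorafenib.

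**Step 4: unequal true failure.** Assume 0.4 with the procedure and 0.7 with sorafenib. The true OR is (0.7/0.3)/(0.4/0.6) = 3.50. With sorafenib q = 0, procedure q = 0.1, 0.3, 0.5 and 0.7 gives recorded failure of 0.46, 0.58, 0.70 and 0.82, and OR 2.74, 1.69, 1.00 and 0.51. A real difference can be hidden or reversed if delivery admissions are common enough.

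**Step 5: do other parts of the plan repair it?** The Data analysis section adjusts for surgical intervention and number of interventions. That conditions on the exposure that generates the spurious event and leaves the outcome as defined. Reporting time to failure by item would expose the hospitalization component, but the composite would still contain it.

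**The case against.** The strongest reply is that the defect depends on the reading. If both an admission and an emergency visit are needed, an elective admission alone never counts and the distortion in Steps 2 to 4 disappears. That is correct, and it means no one can say flatly that any HCC-related hospitalization is a failure. It does not rescue the definition, because that reading drops emergency admissions that belong in the count.

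Second, this is a condensed article, and rules for qualifying admissions often sit in the full protocol or analysis plan. That would answer a complaint about missing detail. Here, however, Table 1 prints a definition which, applied as written, gives an unsound event under either reading.

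Third, a reader might infer that surgery fails simply by being given. The documents do not support this. It would require the index admission to count against the treatment it delivers, and with no start date for time to failure that is undetermined. Repeat sessions are the firmer case.

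Fourth, a reader might infer that the bias favours sorafenib. The article does not give the care setting of any treatment or any admission rate. Its Comparator groups section also lets sorafenib treatment include other interventions within 21 days, so that group can have procedure admissions of its own. Step 3 shows that the direction can vanish or reverse.

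Fifth, reporting by item and collecting both treatments and hospitalizations would make a hospitalization-driven difference partly visible. That lowers the severity but does not correct the composite.

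**Conclusion.** The point stands in conditional form. The printed definition fits neither reading of its hospitalization item, and it feeds a comparison between treatments. If the two items are alternatives, the bias goes against the treatments with more delivery admissions. It favours sorafenib only if its patients have fewer such admissions, which the documents do not state.

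The possible distortion is large: a true OR of 1.00 becomes 0.54 at 50% true failure, with 30% counted delivery admissions on one side and none on the other. That figure rests wholly on assumed rates and shows what could happen, not what will. The severity is moderate: one component of one secondary end point is affected, and overall survival is not.

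**What to change.** - Reword the item to *unplanned HCC-related hospitalization or emergency room visit*.
- State that admissions to give, complete or repeat the planned index treatment, and scheduled assessment admissions, do not count. This also settles the index surgical admission.
- Start time to treatment failure at treatment initiation, in line with the other Table 1 rows.
- Apply the same rule to the rate and to the time to failure.
- Where charts cannot show whether an admission was planned, classify it by treatment dates. Add a sensitivity analysis with those admissions handled the other way.

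The cost is one definition change and a planned/unplanned flag on the hospitalization record, or an algorithm based on treatment dates. The downside is some classification work and possible misclassification, especially in records collected retrospectively.
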